### Recruitment

Patients for the JAY trial will be recruited from (1) the outpatient units of the Department of Child and Adolescent Psychiatry and of CEKIP at the University Hospital Cologne, and (2) paediatric and psychiatric practices in Cologne, Germany.

## Allocation

### Sequence generation

The study will involve randomly allocating participants to different treatment groups. In the experimental group, 35 patients will receive traditional CBT supplemented by the JAY app [67]; in the control group, 35 patients will receive CBT without the app, using traditional paper-and-pencil homework. Participants will be randomized using computerized block randomization with a block size of four.

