**Fig. 1 Fig1:**
[figure not shown]
Study design of the JAY trial

Following these sessions, patients will be randomly allocated to one of the two treatment arms. After randomization, a baseline phase will take place, followed by the T1 assessment. In the subsequent treatment phase, patients in both groups will receive state-of-the-art CBT. In the treatment group (CBT + JAY), homework and assessments will be conducted through the JAY app, while in the active control group (CBT), equivalent tasks will be completed on paper. Each treatment phase will consist of eight sessions with the patient and up to four sessions with a caregiver. The first treatment phase will be followed by the T2 assessment. The final main assessment (T3) will take place after the second treatment phase. Depending on the clinical significance of remaining internalizing symptoms, patients will then either continue with a third treatment phase, which will be followed by the T4 assessment, or the intervention will be stopped and they will proceed to a first follow-up assessment after 8 weeks (T4). A subsequent follow-up evaluation (T5) for all patients will be scheduled 6 months after T4.

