## Participants, interventions, and outcomes

### Study setting

The JAY trial will be a single-center study located at the Center for Child and Adolescent Cognitive Behavior Therapy (CEKIP), Faculty of Medicine and University Hospital Cologne, University of Cologne.

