
### Participant timeline

The participant timeline and measurement schedule for the JAY trial will include four key stages: a screening process, a baseline phase, an intervention period, and a follow-up assessment. The screening process will assess whether families meet the study’s inclusion and exclusion criteria in several steps. First, families will be contacted by telephone for a brief standardized screening. If the initial criteria are met, the patient and a caregiver will be invited for an in-depth screening and information session. Participants who agree to join the study will complete initial questionnaires and undergo three diagnostic sessions to thoroughly assess eligibility (T0). This will be followed by randomization to the experimental or control group. After this, three sessions will be conducted to introduce the patient to their therapist, focusing on building a strong patient-therapist relationship and providing psychoeducation.

The screening process will be followed by a baseline phase that does not include any sessions with the study staff or therapist. Participants will use the JAY app [67] or paper-and-pencil sheets for the purpose of self-observation.

The pre-treatment assessment (T1) will mark the end of the baseline and beginning of the treatment phase. The first part of the treatment phase will involve eight sessions of cognitive-behavioural therapy and up to four sessions with caregivers, followed by an intermediate assessment (T2). The second part of the treatment phase will likewise consist of eight patient sessions and up to four caregiver sessions. Subsequently, another main assessment (T3) will follow. Non-responders to the treatment will be identified using the Internalizing scale from the YSR/11-18R [69] and will continue to receive CBT in a third part of the treatment phase. This will then be followed by a final assessment (T4). Responders to the treatment, as indicated by a lack of significant internalizing symptoms at the main assessment (T3), will conclude their participation in the study. Eight weeks after the final therapy session, they will engage in an initial follow-up assessment (T4).

Finally, every family will complete a follow-up survey (T5) 6 months after T4.

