### Sample size

This study will include *N* = 70 adolescents (35/35) in order to explore the impact of smartphone-augmented CBT on therapy homework adherence among adolescents with depressive and anxiety disorders. Based on a recent systematic review [49], which analyzed the effects of adjunctive apps on therapy across 19 studies, the sample size of 70 in our study lies within the range of reported sample sizes, thus providing a solid basis for comparing the efficacy of adjunctive mobile applications in therapeutic settings. Additionally, a study employing a comparable methodology, which involves a comparison of two groups of 35 participants over four evaluation periods (including before treatment, after treatment, and follow-up assessments), anticipates moderate impacts of their app specifically on therapy homework adherence. For the comparison between groups across four measurement time points, a power analysis indicated a power of 0.84 with a sample size of 35 per group (app vs. no app) at an α level of 0.5 [66]. Additionally, the statistical power of a sample can be enhanced through a large number of observations per participant [34, 92]. In our research, THA will be evaluated for a minimum of three homework tasks per week over approximately 16 weeks.

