### Concealment mechanism

Allocation concealment will be ensured, as randomization will only take place after consent has been obtained from both caregivers and patients and it is confirmed that all inclusion and exclusion criteria are fully met.

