### Implementation

The principal investigator (PI) will supervise the randomization. Recruitment staff, who are responsible for initial evaluations, will begin this process. Next, the PI will return a digital form to the staff indicating the participant’s assigned group. The staff will then inform both the therapist and the family about the treatment details.

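### The stated mechanism does not ensure allocation concealment, and the protocol article places randomisation both after and before the therapist-introduction sessions

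*Protocol article*

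**What the plan says.** All references are to the protocol article.

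**Sequence and concealment.**
- Sequence generation: patients are allocated by "computerized block randomization with a block size of four". No second block size and no stratification factor is named.
- Study setting: "The JAY trial will be a single-center study".
- Concealment mechanism: "Allocation concealment will be ensured, as randomization will only take place after consent has been obtained" and once every inclusion and exclusion criterion is confirmed as met. No other basis for concealment is given.
- Implementation: the recruitment staff who do the initial evaluations start each randomisation, and the principal investigator returns a form to them with the assigned group. Then: "The staff will then inform both the therapist and the family about the treatment details".
- Blinding and Informants: participants, parents, therapists and the assessing clinician are all unblinded.

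**Point of randomisation.**
- Trial design lists the diagnostic sessions and the sessions that introduce the therapist. The text under Fig. 1 then continues: "Following these sessions, patients will be randomly allocated to one of the two treatment arms".
- Participant timeline puts randomisation straight after the T0 diagnostics and goes on: "After this, three sessions will be conducted to introduce the patient to their therapist".

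**The concern.** Concealment means that those who enrol patients cannot foresee the next assignment. Randomising late, after consent and eligibility, is good practice, but it does not prevent foresight. With one constant block size, anyone who sees the running assignments can work out how each block must end. Here the people who evaluate candidates see all of them.

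Some eligibility criteria call for judgement, such as willingness and ability to take part, or whether a comorbid disorder is severe and predominant. Willingness is plausibly related to homework adherence, which is the primary outcome. If enrolment decisions or their timing were influenced by a foreseen arm, the arms could differ at entry on what the trial measures.

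The conflict over the order is a separate matter. According to the Discussion, the introductory sessions were added after a pilot in which adherence fell, and they include psychoeducation about what the app adds to therapy. If they follow randomisation, they are delivered with the arm known. If they precede it, future control patients hear the same material, and anyone who leaves during them is never randomised.

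**Working it through.** The article gives no predictability figure, so there is none to reproduce.

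**Inputs.** Block size 4 (Sequence generation); 1:1 allocation and N = 70 (Sample size); one centre (Study setting). Assumed: one running unstratified sequence, and an observer who knows the block size and every earlier assignment.

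**One block of four.** The six equally likely sequences are AABB, ABAB, ABBA, BAAB, BABA and BBAA.

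| Position | Chance the assignment is certain | Chance the best guess is right |
|---|---|---|
| 1 | 0 | 1/2 |
| 2 | 0 | 2/3 |
| 3 | 1/3 (first two equal: 2 of 6) | 1/3 × 1 + 2/3 × 1/2 = 2/3 |
| 4 | 1 | 1 |
| Sum | 4/3 | 17/6 |

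Per block, 4/3 ÷ 4 = 33.3% are certain, and 17/6 ÷ 4 = 70.8% are guessed correctly.

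**Seventy patients.** 70/4 = 17.5, so there are 17 full blocks and two patients in an eighteenth.
- Certain: 17 × 4/3 + 0 = 22.7, and 22.7/70 = 32.4%. Each full block gives one or two certain assignments, so the possible range is 17 to 34.
- Guessed correctly: 17 × 17/6 + (1/2 + 2/3) = 49.3, and 49.3/70 = 70.5%.
- A simulation of the fixed block gave 32.5% and 70.4%, in agreement.

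**Varying block sizes.** The same simulation used randomly varying sizes and an observer who knows the set of possible sizes and all past assignments.

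| Sizes | Certain | Best guess right |
|---|---|---|
| 4 only (exact) | 32.4% | 70.5% |
| 2, 4, 6 | 4.1% | 70.1% |
| 4, 6 | 5.4% | 69.2% |
| 4, 6, 8 | 2.3% | 67.8% |

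A larger fixed block helps less: 25% of assignments are certain with size 6, and 20% with size 8.

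**Order of randomisation.**
- Trial design with the text under Fig. 1: T0 questionnaires, diagnostic sessions, introductory sessions, randomisation, baseline phase, T1.
- Participant timeline: T0 questionnaires and diagnostic sessions, randomisation, three introductory sessions, baseline phase, T1.

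These cannot both hold. The Discussion says only that the sessions come before the baseline phase, and Concealment mechanism says only that randomisation follows consent and eligibility. Both statements fit either order, so neither settles the matter.

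**Effect on the ITT set.** Analyses of primary endpoint defines the set as randomised patients with a valid baseline assessment, without naming the time point. Informants and the demographics section treat T0 as baseline; the baseline phase ends at T1.

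| Patient leaves during the introductory sessions | Baseline = T0 | Baseline = T1 |
|---|---|---|
| Randomised before the sessions | in ITT | not in ITT |
| Randomised after the sessions | not randomised | not randomised |

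The order therefore changes ITT membership only if baseline means T0. No loss rate is given. For an assumed loss of 5% to 10% of 70, that is 3.5 to 7 patients; if baseline means T1, it is none.

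**The case against.** A reader might infer that allocation in this trial is not concealed, or that staff do foresee a third of assignments. The documents do not support that.
- Foresight needs someone who knows the block size and keeps a full tally. Nothing shows that anyone does.
- Assignments are returned by the principal investigator after eligibility is confirmed, which gives real, if partial, protection. Who generates and holds the list may be in the full protocol, and the article's silence on that is no fault.
- Therapists are not said to learn every allocation. Implementation has them told about their own patient. Only the recruitment staff see all of them.
- One unstratified sequence is an assumption. With strata, an observer would have to keep a tally for each.
- It is not known whether the article, and with it the block size, became public while recruitment was open.
- Several visits lie between telephone screening and randomisation, and another patient can take the foreseen place. At screening, 32% is therefore a ceiling.

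All of this stands, and it limits the point to what the stated mechanism can guarantee. It does not rescue the claim that timing ensures concealment.

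It is also fair to say that varying blocks hardly change the best-guess rate. Their gain is in the share of certain assignments.

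On the order of events, it would go too far to say that T1 changes its meaning. In both accounts T1 follows randomisation and a baseline phase on app or paper, and T0 precedes randomisation. The contradiction itself is not open to dispute.

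**Conclusion.** The point holds in two parts.

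1. Concealment is not ensured by the mechanism given. With a fixed block of four and recruitment staff who receive every assignment, up to about 23 of 70 assignments (32%) could be known in advance and about 70% guessed, against 50% by chance. This is an upper bound. It rests on a single unstratified sequence and on staff who know the block size and track the assignments. It measures vulnerability and is not evidence of selection.
2. The two accounts of when randomisation occurs contradict each other. Which one is followed decides who is randomised and whether the introductory sessions are given with the arm known. If baseline means T0, it also decides whether patients lost in those sessions belong to the ITT set. The number affected cannot be derived from the documents.

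**What to change.** - **Remaining patients.** For those not yet randomised, use randomly varying, undisclosed block sizes (for example 2, 4 and 6), with the list held by someone not involved in recruitment or therapy. The principal investigator, who returns the assignments, also supervises the therapists. Expect the certain share to fall to about 4%, with the best-guess rate still at about 68–70%.
- **Concealment mechanism.** Reword it so that concealment rests on the sequence being hidden from those who enrol, with the timing rule kept as an addition.
- **Order.** Reconcile Trial design, the text under Fig. 1 and Participant timeline to one randomisation point that matches actual conduct, and record which order was used for patients already enrolled. This review does not propose an order or any change to session content.
- **ITT set.** State whether T0 or T1 is the valid baseline.

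The cost is a new list for the remaining patients, some rewording, and a slight extra chance of unequal arms. The present scheme does not guarantee 35/35 either: with two patients in the last block, exact balance has probability 4/6 = 2/3, and otherwise the split is 36/34. Recruitment was planned to finish in March 2026. If it has finished, the new list no longer applies, but the other three items still do.

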### Concealment mechanism

Allocation concealment will be ensured, as randomization will only take place after consent has been obtained from both caregivers and patients and it is confirmed that all inclusion and exclusion criteria are fully met.

### Implementation

The principal investigator (PI) will supervise the randomization. Recruitment staff, who are responsible for initial evaluations, will begin this process. Next, the PI will return a digital form to the staff indicating the participant’s assigned group. The staff will then inform both the therapist and the family about the treatment details.

## Blinding

Due to the nature of the intervention, participants, parents, and therapists cannot be blinded to group allocation. However, the study’s specific hypotheses will be concealed from the caregivers and patients.

## Data collection and management

### Data collection methods

Questionnaire data from both the adolescents and the parents will be collected electronically using the online survey tool LimeSurvey [93]. The data will be exported from LimeSurvey by a designated study staff member and stored in a secure data network. The datasets will be organized by measurement time points and informant (adolescents or caregivers).

Data collected in paper-and-pencil form include the patient’s adherence, assessed using the clinician-rated Adherence Questionnaire as well as the patient-rated individual problem list and retrospective mood assessment. One designated study staff member will digitally input these data. Regular reviews of completeness, consistency, and plausibility will be conducted by two study staff members.

### Informants

In the JAY trial, informants will include the adolescent patient, their caregiver, and an unblinded clinician. Patients will undergo diagnostic sessions and cognitive-behavioural psychotherapy, and will use the JAY app to record mood and for diary activities. Furthermore, they will complete several self-report questionnaires at all measurement time points. The caregiver may be the biological parent or the child’s guardian. Caregivers will be involved in the study by participating in the in-person screening and information sessions along with the patients. They will complete caregiver-report questionnaires at all measurement time points. The unblinded clinician will be a study staff member who works in the area of diagnostics or therapy, or alternatively, a child and adolescent therapist from the Center for Child and Adolescent Cognitive Behavior Therapy (CEKIP). The unblinded clinician may also serve as the adolescent’s therapist which applies to both baseline (T0) and post-treatment (T3) assessments. The clinician will assess the patient’s symptoms based on information gained in the interviews during the diagnostic sessions.

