The following hypotheses will be investigated:The experimental group (CBT + JAY) will show a significantly higher overall THA score compared to the active control group (CBT) throughout the intervention phases, as assessed by quantitative aspects of therapy homework (relative ratio of completed and required entries) as well as qualitative aspects which together as a composite score constitute the primary outcome. The qualitative aspects (content fit, thoroughness, competence of behaviour/thoughts, and clinical relevance) will be evaluated by multiple independent raters using a rating system that defines the assessment criteria.The experimental group (CBT + JAY) will show higher THA compared to the active control group (CBT) as assessed using the clinician-rated Questionnaire for Therapy Adherence after each therapy session [68].The experimental group (CBT + JAY) will show a greater reduction in internalizing symptoms compared to the active control group (CBT) according to self-rating, as measured using the Internalizing Problems scale of the Youth Self-Report 11–18 (YSR/11-18R) [69, 70] as well as the self-report symptom checklists for anxiety (SCL-AD-S) and depression (SCL-DEP-S) from the “Diagnostic system for mental disorders based on ICD-10/DSM-5 for children and adolescents” (DISYPS-III) [71] and using an individual problem list.The experimental group (CBT + JAY) will show a greater reduction in internalizing symptoms compared to the active control group (CBT) according to caregiver rating, as measured using the Internalizing Problems scale of the caregiver-report Child Behaviour Checklist (CBCL/6-18R) [69, 70] as well as the caregiver-report scales for anxiety (SCL-AD-P) and depression (SCL-DEP-P) from the DISYPS-III [71].The experimental group (CBT + JAY) will show a greater reduction in internalizing symptoms compared to the active-control group (CBT) according to clinical rating, as assessed by a clinician using a structured clinical interview (ILF-INTERNAL) from the DISYPS-III [72].The experimental group (CBT + JAY) will show a stronger reduction in comorbid symptoms as measured using the scales Externalizing Problems and Total Problems of the self-report YSR/11-18R and the caregiver-report CBCL/6-18R [69, 70].Patients in the experimental group (CBT + JAY) will show a greater improvement in quality of life, sense of global self-worth, and emotion regulation strategies according to self-report compared to patients in the control group (CBT), as assessed by the Revised Questionnaire for Health-Related Quality of Life Assessment in Children (KINDL^R^) [73], by a modified German version of the Self-Perception Profile for Children called the Harter scale [74, 75], and by a modified version of the Questionnaire to Assess Children’s and Adolescents’ Emotion Regulation Strategies (FEEL-KJ) [76], respectively.Patients in the experimental group (CBT + JAY) will show greater treatment satisfaction than those in the control group (CBT), as measured by a modified version of the self-report Client Satisfaction Questionnaire (ZUF-8-M patient) [77, 78].

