#### Secondary outcomes

Secondary outcomes include:The quantity of therapy homework, as assessed by the relative ratio of completed to requested entries within the JAY app or on the paper-and-pencil sheets between the treatment sessions.Quality of the entries, as rated by a pool of clinicians based on the app entries or the homework sheets according to the rating system mentioned in the previous section.Patient-rated symptoms of anxiety and depression, assessed by the Internalizing Problems scale of the self-report YSR/11-18R [69, 70] as well as the self-report scales for anxiety (SCL-AD-S) and for depression (SCL-DEP-S) from the DISYPS-III [71]. Reliability and validity as well as sensitivity to change of the German version of the YSR/11-18R and the DISYPS-III scales have already been demonstrated in German samples [70, 71]. The Internalizing Problems scale of the YSR/11-18R will be assessed at every measurement time point and the SCL-AD-S and SCL-DEP-S will be assessed at T0 and T3.Caregiver-rated symptoms of anxiety and depression, assessed by the Internalizing Problems scale of the caregiver-report CBCL/6-18R [69, 70] as well as the caregiver-report scales for anxiety (SCL-AD-P) and for depression (SCL-DEP-P) from the DISYPS-III [71]. Reliability and validity as well as sensitivity to change of the German version of the CBCL and the DISYPS-III scales have already been demonstrated in German samples [70, 71]. The Internalizing Problems scale of the CBCL/6-18R will be assessed at every measurement time point, and the SCL-AD-P and SCL-DEP-P will be assessed at T0 and T3.Clinician-rated symptoms of anxiety and depression based on the ILF-INTERNAL from the DISYPS [72], assessed at T0 and T3.Individually defined problem behaviours were rated by the patients using an individual problem list (IPL) in every therapy session. The problem list allows for the assessment of four targeted issues, rated on a 5-point Likert scale, and of the burden of the problems, rated on a 10-point Likert scale. Individual problem lists have been shown to be reliable, valid, and sensitive to change [85].Patient- and caregiver-rated comorbid symptoms and overall behavioural and emotional problems, measured using the remaining scales Externalizing Problems and Total Problems of the self-report YSR/11-18R and the caregiver-report CBCL/6-18R [69, 70]. Reliability and validity as well as sensitivity to change of the German version of these scales have been demonstrated in German samples [70]. These outcomes will be measured at T0 and T3.Patients’ adherence during the weekly therapy sessions (e.g., engagement in tasks and activities) will be measured using the clinician-rated Adherence Questionnaire [68], which will be assessed after every therapy session. This was adapted from the AUTHARK trial [41], in which good internal consistencies were reported.Quality of life, assessed using the Revised Questionnaire for Health-Related Quality of Life Assessment in Children and Adolescents (KINDL^R^) [73], which evaluates aspects related to physical and psychological well-being, the adolescent’s self-worth, as well as friendships and family relationships. Reliability and validity as well as sensitivity to change of scale have been demonstrated in German samples [86, 87]. This outcome will be assessed at T0 and T3. Sense of global self-worth, assessed using a modified German version of the Self-Perception Profile for Children, called the Harter scale [74, 75], which evaluates perceptions of cognitive and physical competence, peer acceptance, physical appearance, and self-worth. Reliability and validity of the original scale were demonstrated in a German clinical sample [88]. This outcome will be assessed at T0 and T3. Emotion regulation strategies were assessed using a modified version of the Questionnaire to Assess Children’s and Adolescents’ Emotion Regulation Strategies (FEEL-KJ) [76], which evaluates adaptive and maladaptive strategies to regulate feelings of anxiety and sadness. Reliability and validity have been demonstrated [76]. This outcome will be assessed at T0 and T3. Retrospective mood assessments will be conducted in every week in which the patient has used the momentary assessment of the JAY app or the paper-and-pencil equivalent. All 16 momentary affective and mental states assessed during the week will be rated retrospectively for the same week on a scale from 0 to 100. Patient-rated satisfaction with the treatment, assessed using a modified version of the self-report Client Satisfaction Questionnaire (ZUF-8-M patient) [77, 78], which has been shown to be reliable, valid, and sensitive to change [89]. Satisfaction will be assessed once, at T3. Patient-rated usability of the JAY app, assessed using a German translation of the System Usability Scale (SUS), which has been shown to be reliable, usable, and valid [90]. The scale measures effectiveness, efficiency, and satisfaction of and with a system. Usability will be assessed for patients in the experimental group once, at T3. Life events in the domains of school, family, and friendships as well as illness, accidents, and losses, as measured by the Zurich Life-Event List (ZLEL), which has been shown to be reliable and valid [91]. This measure will be applied once, at the follow-up (T5) in this study.

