The app should be acceptable and user-friendly for adolescents, as otherwise, it could lead to low adherence, frustration, and disengagement among participants. In a smaller pilot study, the app was deployed in therapy sessions with adolescents and their therapists. In qualitative interviews, both parties reported that the app was user-friendly, intuitive, and appropriate for its purpose. It was noted that the introduction of a smartphone app altered the dynamics of the therapist-patient relationship, and patients perceived the app as a replacement for human interaction. This led patients to feel less connected to and supported by their therapist, and adherence to the therapy and the research protocol decreased. To overcome this problem, three sessions with the therapist were integrated into the study design, which precede the baseline phase and focus on building the foundation for a strong therapist-patient relationship and psychoeducation about the complementary role and benefits of the app.

Another important aspect to be considered is data privacy. To prevent a threat to confidentiality, apps should not make patients’ data available to third parties, and the transfer of data to the therapist should only take place with the patient’s informed consent [50, 56]. For this reason, participants will have full control over their data, which will be stored locally on their smartphones. Participants will decide themselves which data to share by uploading them to a secure research server.

Further methodological challenges include a potential bias due to the inability to blind patients and therapists to the interventions. In addition, the unblinded clinician responsible for the outcome assessment during the clinical interviews may also serve as the treating therapists, which could increase the risk of assessment bias. Participants will not be informed about the study hypotheses. Nevertheless, the information they receive may lead them to perceive the JAY app as innovative and anticipate higher adherence to therapy homework. Similarly, therapists may introduce bias when evaluating the therapy homework. In future studies, it is important to consider incorporating independent blinded evaluation of therapy homework adherence into the study design in order to mitigate potential biases.

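### The treating, unblinded therapist may conduct the T3 interview that alone tests secondary hypothesis 5, and the acknowledged rater bias has no planned countermeasure

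*Protocol article*

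**What the plan says.** The fifth hypothesis in the Background predicts a larger symptom reduction in the app arm "according to clinical rating, as assessed by a clinician using a structured clinical interview (ILF-INTERNAL) from the DISYPS-III". Under Secondary outcomes the measure is listed as "Clinician-rated symptoms of anxiety and depression based on the ILF-INTERNAL from the DISYPS [72], assessed at T0 and T3". No other instrument serves this hypothesis.

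The Informants section says that "informants will include the adolescent patient, their caregiver, and an unblinded clinician". It describes this clinician as "a study staff member who works in the area of diagnostics or therapy", or alternatively a therapist from the same centre, and allows the clinician to be the patient's own "therapist which applies to both baseline (T0) and post-treatment (T3) assessments".

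The Blinding section explains why patients, parents and therapists cannot be blinded. It gives no reason for leaving a separate outcome interviewer unblinded, and it withholds the hypotheses only from patients and caregivers. The Discussion concedes that the assessing clinicians "may also serve as the treating therapists, which could increase the risk of assessment bias". Its suggestion of blinded evaluation concerns homework adherence in future studies, not the symptom interview in this trial.

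**The concern.** The clinician who delivered the app or paper condition may also score the patient's symptoms afterwards, knowing the arm and not being among those from whom the hypotheses are withheld. If such raters expect the app to help, T3 scores can differ between arms without any difference in symptoms.

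Patients and caregivers rate symptoms too, and they cannot be blinded to the intervention. The interview is the one symptom outcome for which a masked rater is at least conceivable, so it could have been the more independent witness. As planned, a positive result for hypothesis 5 cannot be separated from rater expectation.

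**Working it through.** **No stated figure to reproduce.** The protocol gives no size for rater bias. The check has two parts: whether the planned analysis could remove the bias, and how much an assumed bias would matter.

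**1. Where arm-related bias can enter.** Trial design and Participant timeline both place the T0 diagnostic sessions before randomization, so T0 ratings cannot depend on arm. T3 ratings can. Adjusting for T0 does not remove a shift that arises only at T3, and the mixed models or GEE named under Analyses of secondary endpoints would count it as part of the group effect.

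**2. Inputs.**
- n = 35 per arm (Sample size).
- With the attrition of up to 20% in Missing data: 35 × 0.8 = 28 per arm.
- Two-sided 5% test, true app effect zero (assumptions).
- Rater shift b towards the app at T3, in SD units, averaged over all interviews in the arm (assumption, shown as a range).

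**3. Formula.** For a two-sample t test, df = 2n − 2 and the noncentrality is b × √(n/2). The chance of a significant result favouring the app is the upper-tail probability of the noncentral t beyond the 97.5% point of the central t.

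| b (SD) | Noncentrality, n = 35 | Favours app, n = 35 | Favours app, n = 28 |
|---|---|---|---|
| 0 | 0 | 2.5% | 2.5% |
| 0.1 | 0.1 × √17.5 = 0.42 | 6.1% | 5.6% |
| 0.2 | 0.84 | 12.8% | 11.0% |
| 0.3 | 1.25 | 23.5% | 19.6% |

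Counting significant results in both directions at n = 35 gives 5.0%, 7.0%, 13.1% and 23.6%. The one-direction figures are the relevant ones here, because the worry is a false result in favour of the app.

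**4. Dilution.** The overlap is permitted, not required. If only a fraction p of interviews is done by the treating therapist, and only those are shifted by b, the arm-wide shift is p × b. With p = 0.5 and b = 0.2, it is 0.5 × 0.2 = 0.1 SD, so the chance is about 6% and not 13%. The documents do not give p.

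**The case against.** **The choice is disclosed.** The protocol calls the rater unblinded, names the overlap and lists it as a limitation. This is correct: nothing is hidden or contradicted. Disclosure tells readers to be cautious, but it does not reduce the bias or show afterwards which ratings were exposed to it.

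**The outcome is secondary and has parallels.** This also stands. The primary adherence score does not use the interview. Hypotheses 3 and 4 test internalizing symptoms by self-report and caregiver report, so an effect seen only by clinicians would stand out. The cross-check is partial, because those informants also know the arm. The structured interview limits the rater's discretion but does not abolish it.

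**Self-interest is not arm-related.** A reader might infer that therapists judging their own results must bias the comparison. The documents do not support this. Both arms receive CBT from therapists who may rate their own patients, so that interest exists on both sides. Only an expectation about the app differs by arm, and neither its size nor its direction is known. The Discussion reports that pilot patients felt less connected to their therapist when the app was used, so a shift in favour of the app cannot be presumed.

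**A different interviewer is not automatically blinded.** A reader might infer that the listed pool makes the bias wholly avoidable. It does not. Informants labels every permitted rater unblinded. Elsewhere, staff relay the allocation (Implementation), give app training and technical help (Intervention description) and scan paper homework (Data management), all at one centre. Exchanging therapists without masking would leave the expectation about the app in place.

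**Conclusion.** The point holds as a weakness in one secondary outcome. The plan permits the treating, unblinded therapist to produce the only data for hypothesis 5 at T3, states that this may bias the result, and does nothing to limit it. The reason given for not blinding therapists does not extend to a separate interviewer.

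The size is unknown. The figures of about 6%, 13% and 24%, against 2.5%, assume no true effect, 35 per arm and an arm-wide shift of 0.1, 0.2 or 0.3 SD. They show sensitivity and do not estimate this trial's error rate. The stronger conclusion, that a positive hypothesis 5 result must be an artefact or that the trial's main conclusion is compromised, does not follow.

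**What to change.** **For T3 interviews still to be done,** amend Informants so that the interviewer:
- comes from the pool already listed;
- is not that patient's therapist;
- had no part in relaying that patient's allocation, in app support or in handling the homework;
- is not told the arm, as far as is feasible.

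Ask the patient not to mention app or paper during the interview.

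**For all T3 interviews, including those already done,** record who conducted the interview (own therapist or not) and any unmasking. Repeat the hypothesis 5 analysis without own-therapist ratings. Report hypothesis 5 as supportive evidence wherever the rater was unblinded.

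**Cost.** Protocol wording, scheduling and one extra data item. Participant timeline already plans two patient visits for the T3 interview, so no visit is added, and the raters come from existing staff. There are four downsides:
- The interviewer knows the patient less well.
- The rater may change between T0 and T3.
- Recruitment began in October 2023 and was planned to end in March 2026, so the change may reach only later interviews, and ratings before and after it will differ in rater regime.
- Masking may sometimes fail at a single centre.
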